## Abstract

**Introduction:**

Uncomplicated urinary tract infections (uUTIs) in women are common infections encountered in primary care. Evidence suggests that rapid point-of-care tests (POCTs) to detect bacteria and erythrocytes in urine at presentation may help primary care clinicians to identify women with uUTIs in whom antibiotics can be withheld without influencing clinical outcomes. This pilot study aims to provide preliminary evidence on whether a POCT informed management of uUTI in women can safely reduce antibiotic use.

**Methods and analysis:**

This is an open-label two-arm parallel cluster-randomised controlled pilot trial. 20 general practices affiliated with the Bavarian Practice-Based Research Network (BayFoNet) in Germany were randomly assigned to deliver patient management based on POCTs or to provide usual care. POCTs consist of phase-contrast microscopy to detect bacteria and urinary dipsticks to detect erythrocytes in urine samples. In both arms, urine samples will be obtained at presentation for POCTs (intervention arm only) and microbiological analysis. Women will be followed-up for 28 days from enrolment using self-reported symptom diaries, telephone follow-up and a review of the electronic medical record. Primary outcomes are feasibility of patient enrolment and retention rates per site, which will be summarised by means and SDs, with corresponding confidence and prediction intervals. Secondary outcomes include antibiotic use for UTI at day 28, time to symptom resolution, symptom burden, number of recurrent and upper UTIs and re-consultations and diagnostic accuracy of POCTs versus urine culture as the reference standard. These outcomes will be explored at cluster-levels and individual-levels using descriptive statistics, two-sample hypothesis tests and mixed effects models or generalised estimation equations.

**Ethics and dissemination:**

The University of Würzburg institutional review board approved MicUTI on 16 December 2022 (protocol n. 109/22-sc). Study findings will be disseminated through peer-reviewed publications, conferences, reports addressed to clinicians and the local citizen’s forums.

**Trial registration number:**

ClinicalTrials.gov NCT05667207.

Strengths and limitations of this studyThis study will inform the design and conduct of future confirmatory randomised controlled trials (RCTs) to evaluate the effects of a point-of-care test-guided management strategy on the use of antibiotics in women with suspected uncomplicated urinary tract infection in primary care settings.The open-label cluster-RCT design implies that participants cannot be identified before randomisation, thus, post-randomisation recruitment may represent a source of selection bias.The execution and interpretation of microscopy test results may potentially differ across medical assistants, affecting diagnostic accuracy measurements and treatment outcomes. This will be counteracted by providing all intervention practices with standardised ad hoc competency-based training.

## Introduction

Uncomplicated urinary tract infections (UTIs) are a common reason for adult women to consult a healthcare professional and a major driver of antibiotic prescriptions in the community.^1^ Up to 95% of women presenting to their general practitioner (GP) receive antibiotics, despite uncomplicated UTIs (uUTIs) being self-limiting in up to 50% of cases.^1 2^

As antibiotic prescriptions are closely related to the emergence of resistant micro-organisms, reducing unnecessary use of these drugs in uUTI management is important to counteract the rise of antimicrobial resistance.^3–5^

Randomised controlled trials (RCTs) have been conducted to establish whether alternatives to immediate antibiotic treatment, such as delayed prescriptions, herbal formulations or non-steroidal anti-inflammatory drugs reduce antibiotic use without significant patient harm.^6–11^ All strategies were highly effective in reducing antibiotic use over usual care. Nonetheless, if compared with immediate antibiotics, the alternative treatment strategies showed an increased risk of longer symptom duration, higher symptom burden, incomplete recovery, febrile UTI, pyelonephritis and antibiotic use at follow-up.^12^

A recent meta-analysis of RCTs confirmed these findings analysing individual participant data of 3524 patients from eight primary care trials.^13^ In addition, the authors focused on prognostic and moderating factors of treatment effects. They found that, in women treated without antibiotics, incomplete recovery was more likely if, at baseline, erythrocytes were found in urine and women had a positive urine culture (OR 4.68, Bayesian credible interval (CI) 2.07 to 10.77). If only the urine culture was positive, an incomplete recovery was likely with OR 2.24 (CI 1.00 to 5.17), while if only the test for erythrocytes was positive the OR was 2.60 (CI 1.086 to 32). In contrast, the authors found no significant difference in the likelihood of incomplete recovery between non-antibiotic strategies and immediate antibiotics if both tests were negative (OR 0.82, CI 0.331 to 95). Moreover, positive urine culture results and erythrocytes in urine were found to be independent predictors of complications such as pyelonephritis, febrile UTI and of antibiotic use at follow-up.^13^

These findings show a clear benefit of immediate antibiotics in all cases in which the woman’s urine culture is positive, and erythrocytes are found in urine. Simple and affordable tests exist to detect erythrocytes at the point-of-care (POC) rapidly, namely urinary dipsticks^14^; however standard urine cultures are not useful for immediate clinical decisions, as they require 48 hours or more to provide definitive results.^15–17^ This led to studies evaluating portable devices to perform urine culture, which could deliver quicker results than standard cultures and could possibly lead to a more accurate diagnosis than the usual diagnostic approach based only on symptoms and dipstick test results. The multinational POETIC RCT found that POC urine culture and susceptibility testing were not effective at reducing immediate antibiotic prescriptions.^18^ A Danish RCT found that adding POC susceptibility testing to POC-culture was unlikely to improve the appropriateness of treatment decisions in women with uUTI.^19^ One explanation for these poor results may be, that POC-cultures require 24 hours to deliver results and, given the prognostic and moderating effects of a positive urine culture (ie, significant bacteriuria) the treatment decision is best to be made immediately during index consultation.^13^

To date, urine microscopy is the only rapid POC-test (POCT) able to directly detect bacteria in urine that has been evaluated in a general practice setting. Among the various microscopic methods, phase-contrast microscopy does not require centrifugation or other time-consuming specimen preparation methods, thus being easier to implement in practice than other microscopic approaches.^20^ Several studies have investigated its diagnostic accuracy in detecting UTI in adult outpatients and have shown promising, although conflicting results. Reported sensitivity varied between 74% and 95%, while specificity ranged between 63% and 97%.^21–24^ Nevertheless, although a recent systematic review concluded that microscopy ‘seems to be an accurate, valid and feasible screening-test for bacteriuria in patients with symptoms of UTI in general practice’, it acknowledged that there is still a lack of solid evidence supporting its accuracy to diagnose UTIs.^25^

Diagnostic RCTs have the advantage over traditional diagnostic studies of providing information on test accuracy but also on whether the expected differences in accuracy over usual care are clinically relevant.^26^ To date, the effects of a diagnostic and treatment strategy guided by POCTs for bacteria and erythrocytes in urine on antibiotic use in women with suspected uUTI have not been studied. This pilot RCT aims to provide information about the feasibility and sample size of a full-scaled diagnostic RCT in general practice and to provide initial data on the effects of a POCT–guided diagnostic and treatment algorithm on antibiotic use. POCT to be used are phase-contrast microscopy to detect bacteria and urinary dipsticks to detect erythrocytes in urines.

## Methods and analysis

### Design

MicUTI (Microscopy in Urinary Tract Infections) is a pragmatic open-label, two-arm parallel cluster randomised pilot trial. General practices are randomly allocated to either the POCT-based management strategy (intervention) or standard care management. GPs whose practice is allocated to the intervention will have their management guided by phase-contrast microscopy to identify bacteria and urinary dipsticks to identify erythrocytes in urine samples. GPs whose practice is allocated to the control arm will perform usual care, with treatment decisions-based mainly on symptoms and dipstick testing for erythrocytes, leucocytes and nitrites. For the trial duration (6 months), practices are asked to systematically recruit women aged 18–70 years with symptoms suggesting a uUTI (dysuria, frequency/urgency of micturition, nocturia, with or without lower abdominal pain) to be included in the trial.

### Objectives

#### Primary objective

The primary objective of this study is to assess the feasibility of a full-scaled diagnostic RCT. The primary endpoints are patient recruitment efficacy and the percentage of retention in the trial. Recruitment efficacy will be calculated as the number of participants enrolled per site over the 6 months of trial duration, and retention as the percentage of complete follow-ups per site over 28 days. A confirmatory study without major design changes will be considered feasible if study sites recruit 10 patients each and patients lost to follow-up do not exceed 20%.

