### Randomisation of study sites

General practices participating in the trial (hereafter: study sites) will be asked to provide the number of consulting patients over the last year to determine practice size. Study sites of larger size are foreseeably able to recruit more patients for the duration of the trial, so that practice size will be balanced between the two arms (each with 10 practices) using minimisation.^29^ The minimisation algorithm is centrally programmed in Python by the study statistician. To mask the trial statistician (GB) to intervention/control assignments, the minimisation algorithm will be executed by the trial’s statistical consultant based at the Technical University of Munich (AH), who is not involved in the conduction of the trial. Intervention/control assignments of practices will be communicated to the UKW and the FAU, who then will communicate their allocation to the study sites. To minimise selection bias, study sites were identified for inclusion in the trial prior to randomisation.

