#### Statistical analyses

Descriptive statistics will be calculated for all variables per site and as summary measures across sites. Continuous and count variables will be summarised by mean and SD, or median and IQR in case of skewed data. Binary and categorical variables will be summarised through counts and percentages. CIs and prediction intervals will be calculated for the two feasibility endpoints (recruitment efficacy and percentage of retention in the trial) in addition.

We acknowledge that this feasibility RCT is not powered to detect any statistically significant effects. Nevertheless, explorative analyses will be undertaken at the cluster-level and the individual-level to evaluate the effects of the intervention on the secondary outcome variables using two-sample hypothesis tests, random effects models and generalised estimation equations, as appropriate. Alongside point-estimates, p values and 95% CIs will be reported.

Missing data will be explored to understand why they are unavailable; when missing data are due to incomplete follow-up survival or censored regression analyses will be considered, otherwise multiple imputation with chained equations or Bayesian imputation will be applied. The intraclass correlation coefficient will be calculated for the secondary endpoints to inform subsequent sample size and power calculations.

All the analyses will be undertaken using statistical software packages Stan,^36^ R and Stata (StataCorp College Station, Texas, USA: StataCorp).

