#### Sample size considerations

An ad hoc analysis undertaken on claims data provided by the Bavarian health insurance union (Kassenärztliche Vereinigung) covering all diagnosed UTIs in ambulatory care from 2015 to 2019 showed that each GP had an average of 60 encounters for uUTI in women aged 18–70 per year, with only slight seasonal fluctuations (data not shown). Considering that some of these encounters occur in out-of-hours care and that not all of the patients presenting with uUTI are going to be eligible, we expect that 200 patients in both arms (ie, 100 patients per arm=an average of 10 enrolled patients in each of the 20 clusters) is a reasonably achievable sample within 6 months of trial duration.

Assuming that the percentage of complete follow-up is 75% in the population the patients are sampled from, a simulation study showed that the 200 patients of the feasibility trial enable the estimation of the percentage of complete follow-up with a 95% CI of width of less than 13% with a likelihood of 0.90.

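### Retention is defined and summarised per site, but the 20% rule and the precision statement are worded on patients; the plan does not say which figure is judged, and the two can give opposite verdicts.

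*Protocol article*

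**What the plan says.** Four places in the protocol article bear on retention, which is one of the two primary endpoints.

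- **Definition (Primary objective).** The endpoint is first named as a percentage for the trial, then calculated per site: "retention as the percentage of complete follow-ups per site over 28 days".
- **Summary (Abstract, Methods and analysis; Statistical analyses).** The abstract has "retention rates per site, which will be summarised by means and SDs, with corresponding confidence and prediction intervals". The analysis section says "Descriptive statistics will be calculated for all variables per site and as summary measures across sites", and then: "CIs and prediction intervals will be calculated for the two feasibility endpoints (recruitment efficacy and percentage of retention in the trial) in addition".
- **Decision rule (Primary objective).** A confirmatory study without major design changes is considered feasible if "study sites recruit 10 patients each and patients lost to follow-up do not exceed 20" per cent. The rule is worded on patients and names no level of aggregation.
- **Precision (Sample size considerations).** With an assumed 75% complete follow-up, "the 200 patients of the feasibility trial enable the estimation of the percentage of complete follow-up" with a 95% CI narrower than 13 points, with likelihood 0.90.

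On site size, Randomisation of study sites says: "Study sites of larger size are foreseeably able to recruit more patients for the duration of the trial".

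**The concern.** A mean and SD of per-site rates is naturally a summary of 20 site percentages, each counted once. A limit on patients lost, and a precision statement for 200 patients, naturally refer to one percentage over all women. These are different quantities unless every site enrols the same number or retention does not vary with site size. The protocol expects unequal enrolment. Minimisation balances practice size between arms; it does not make sites equal.

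Retention is half of the rule for moving to a confirmatory trial without major design changes. If the figure compared with 20% is not fixed, it can be chosen after the data are seen. The interval reported with the endpoint may also belong to a different quantity from the one judged, with a precision that the sample size section does not describe.

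**Working it through.** **Inputs from the protocol:** 20 sites, 10 women per site on average, N = 200, assumed complete follow-up 75%, 95% CI, target width 13 points, likelihood 0.90, limit 20% lost. Complete follow-up is taken as the complement of loss, so the pass mark is 80%. The protocol gives no ICC and no spread of site sizes; values for these are assumptions.

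**1. Reproduce the stated precision.** Let X ~ Binomial(200, 0.75) be the number of women with complete follow-up, pooled and unclustered. Sum the probability of every X whose 95% CI is narrower than 0.13.

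- Exact (Clopper-Pearson) interval: the width is 13.00 points at X = 142 and 12.94 at X = 143, so the target is met in practice when X is 143 or more. The probability is 0.889, close to the stated 0.90.
- Wald, Wilson, Agresti-Coull and Jeffreys intervals: 0.993 to 0.997.

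The stated figure is therefore right for a pooled, unclustered percentage.

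**2. Same target for the abstract's summary.** For the mean of 20 site percentages, the width is 2 × t(0.975, 19) × SD/√20, with t = 2.093. With equal sites and ICC 0 the typical width is 2 × 2.093 × √(0.75 × 0.25/200) = 12.8 points, already close to 13, so only somewhat more than half of trials meet the target. Simulation (5,000 runs per setting, beta-binomial retention, true value 75%) gives the following probabilities of a width under 13 points:

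| ICC (assumed) | Site mean, 20 sites of 10 | Site mean, unequal sites (CV about 0.65, assumed) | Pooled %, cluster-robust CI, same unequal sites |
|---|---|---|---|
| 0 | 0.57 | 0.12 | 0.62 |
| 0.02 | 0.38 | 0.07 | 0.39 |
| 0.05 | 0.19 | 0.03 | 0.21 |
| 0.10 | 0.06 | 0.01 | 0.08 |

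With equal sites the site mean and the pooled percentage are the same number. The drop from 0.889 to 0.57 therefore comes from estimating the variance between sites on 19 degrees of freedom, not from a different point estimate. The last column shows that a pooled percentage with an interval that allows for clustering also misses 0.90.

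**3. Opposite verdicts by arithmetic alone.** Take 10 sites of 15 women and 10 sites of 5, so N = 150 + 50 = 200.

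- 14/15 and 3/5 complete: pooled (140 + 30)/200 = 85.0%, 15.0% lost, pass; site mean (93.3% + 60.0%)/2 = 76.7%, 23.3% lost, fail.
- 10/15 and 5/5 complete: pooled (100 + 50)/200 = 75.0%, 25.0% lost, fail; site mean (66.7% + 100%)/2 = 83.3%, 16.7% lost, pass.

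**4. How often this could happen.** Assume 20 sites, a mean of 10 women, ICC 0.05, and site sizes that are Poisson or negative binomial with dispersion k = 4, 2 or 1, with no link between site size and retention. Share of 20,000 simulated trials per setting in which the two figures fall on opposite sides of 80%:

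| True retention | Poisson | k = 4 | k = 2 | k = 1 |
|---|---|---|---|---|
| 75% (the plan's value) | 4% | 9% | 12% | 16% |
| 80% | 10% | 19% | 24% | 28% |
| 85% | 3% | 7% | 10% | 13% |
| 90% | under 0.1% | 0.3% | 0.7% | 1.2% |

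The mean absolute gap between the two figures is about 1 to 3 points at 75–80%.

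**5. Which figure is more precise.** At k = 2 and 80% retention, the standard error (site mean v pooled) is 4.4 v 3.8 points at ICC 0.05, 5.4 v 5.6 at ICC 0.20 and 6.0 v 6.5 at ICC 0.30. The order reverses near an ICC of 0.2.

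**The case against.** The strongest reply is that the pooled reading is already available. Both the Primary objective and Statistical analyses speak of retention in the trial, binary variables are to be summarised by counts and percentages, and the analysis section promises figures both per site and across sites. Mean and SD of site rates appear explicitly only in the abstract. No sentence says that the mean is unweighted, and a mean weighted by site size equals the pooled percentage exactly. Weighting and interval method are commonly left to the analysis plan, which is not shown. The trial is a pilot and makes no hypothesis test on retention.

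Much of this stands. A reader might infer that the protocol commits itself to judging an unweighted site mean; its wording does not go that far. A reader might also infer that the definitions would conflict in about a quarter of trials. That holds only with true retention at the threshold and clearly unequal sites. Most such disagreements would be near-threshold results that either figure would leave uncertain. Nor can one say in general that the site mean is less precise, because this depends on an ICC that the protocol does not give.

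The mismatch itself is not removed. If the rule is pooled, the mean, SD and interval named in the abstract do not describe the quantity judged. If the rule is the site mean, the precision statement does not apply to it. The rule could also be read as applying to each site. This is not detail left for later: the statements already made about a primary endpoint refer to different quantities, and none is linked to the 20% limit.

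**Conclusion.** The point holds. The protocol gives a per-site definition and summary of retention together with a patient-level threshold and precision statement, and does not say which figure is compared with 20%. That opposite verdicts are possible needs only unequal site sizes, which the protocol expects, and retention that varies with site size by chance or otherwise. How often they would occur depends on assumed dispersion and ICC: about 10–28% of trials at 80% true retention, about 4–16% at the plan's own 75%, and about 1% or less at 90%.

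The 0.90 is not a miscalculation. It is correct for a pooled, unclustered percentage and does not carry over to an interval built on 20 site percentages (about 0.57 with equal sites and no clustering, lower otherwise). The correction should be made because it concerns a primary endpoint and its progression rule, but it does not threaten the trial.

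**What to change.** In the abstract, the Primary objective and Statistical analyses, state that the 20% criterion is judged on women with complete follow-up divided by all women enrolled, over all sites, with a 95% CI adjusted for clustering by practice. In Sample size considerations, say that the precision statement refers to this percentage, and either restate it for a cluster-adjusted interval under a stated ICC or say that it ignores clustering. Keep the per-site percentages, their SD and the prediction interval as a description of variation between sites.

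The cost is a few sentences and no new data. Large sites will carry more weight in the headline figure, although the per-site figures still show the small ones. The cluster-adjusted interval may be wider than the sample size section suggests: under the assumed unequal sites, the likelihood of a width below 13 points falls to about 0.62 at ICC 0 and 0.21 at ICC 0.05.

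### The recruitment criterion is worded as 10 patients at each site, but 10 is the planned average; taken literally it would almost certainly fail at planned recruitment, and the protocol does not say that the mean is meant

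*Protocol article*

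**What the plan says.** All references are to the protocol article.

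- **Primary objective.** The recruitment endpoint is a count per site: "Recruitment efficacy will be calculated as the number of participants enrolled per site over the 6 months of trial duration". The decision rule comes next. A later trial of essentially the same design "will be considered feasible if study sites recruit 10 patients each"; a second condition caps loss to follow-up at 20%.
- **Sample size considerations.** The planned total is 200, described as "an average of 10 enrolled patients in each of the 20 clusters".
- **Randomisation of study sites.** Unequal counts are expected: "Study sites of larger size are foreseeably able to recruit more patients for the duration of the trial". For that reason "practice size will be balanced between the two arms (each with 10 practices) using minimisation".
- **Abstract, Methods and analysis.** The two feasibility outcomes are to be "summarised by means and SDs, with corresponding confidence and prediction intervals".

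The article does not state whether the threshold of 10 applies to every site, to a share of sites, or to the mean.

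**The concern.** The number that the sample size section uses as a mean reappears in the decision rule as something each site is to reach. A threshold equal to the mean, required of all 20 sites at once, is much harder to meet than the plan itself, particularly when the plan expects sites to differ.

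Feasibility is the primary objective, and this sentence is the only stated rule for judging it. If the wording is taken at face value, a pilot that recruits its planned 200 patients would report that the recruitment criterion was missed. If it is taken as a mean, the same data would meet it. A decision rule should give one answer for one set of counts, and the reading should be settled before the counts are analysed.

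**Working it through.** **Inputs from the article.** 20 practices; planned mean 10 per practice; planned total 200; threshold 10.

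**Inputs assumed.** The article gives no between-site spread. I take sites as independent and use a Poisson count as the base case. For extra variation I use a negative binomial count with a between-site coefficient of variation (CV) of 0.4 to 0.8.

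**Step 1. The plan's own figure.** 20 × 10 = 200 = 2 × 100. The planned total reproduces.

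**Step 2. A check that needs no distribution.** If all 20 sites enrol at least 10, the total is at least 20 × 10 = 200. With a total of exactly 200, the literal criterion is therefore met only if every site enrols exactly 10. One site with 11 forces another below 10.

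**Step 3. The literal reading at the planned mean.** P(all 20 sites reach 10) = P(X ≥ 10)^20.

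| Count model, mean 10 | P(one site ≥ 10) | P(all 20 ≥ 10) |
|---|---|---|
| Poisson | 0.542 | 0.542^20 = 4.8 × 10⁻⁶ |
| CV 0.4 | 0.484 | 5.0 × 10⁻⁷ |
| CV 0.6 | 0.449 | 1.1 × 10⁻⁷ |
| CV 0.8 | 0.416 | 2.4 × 10⁻⁸ |

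Under Poisson, the expected number of sites below 10 is 20 × (1 − 0.542) = 9.2. Less spread than Poisson helps little: with normally distributed counts, rounded, and a between-site SD of only 1 patient, one site reaches 10 with probability 0.691, and 0.691^20 = 0.0006.

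**Step 4. The literal reading above plan.**

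| True mean | Poisson | CV 0.4 | CV 0.8 |
|---|---|---|---|
| 15 | 0.930^20 = 0.23 | 0.767^20 = 0.005 | 0.588^20 = 0.00002 |
| 20 | 0.995^20 = 0.90 | 0.895^20 = 0.11 | 0.694^20 = 0.0007 |

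Under Poisson, an 80% chance of meeting the literal criterion needs a true mean of about 18.6.

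**Step 5. The mean reading.** A mean of at least 10 is the same as a total of at least 200. With a true mean of 10, P(total ≥ 200) is 0.51 (Poisson), 0.50 (CV 0.4) and 0.48 (CV 0.8).

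**Step 6. The readings side by side.** At a true mean of 12 under Poisson, the literal criterion is met with probability 0.758^20 = 0.004 and the mean criterion with probability 0.996. At 20% above plan the two readings almost always disagree.

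**The case against.** The best reply is that the authors meant the mean. The sentence does not say every site, at least, or minimum. The sample size section uses the same number with the word average, the abstract summarises the outcome by means and SDs, and the randomisation section shows that nobody expected equal counts. On this view the remedy is one clarifying word, and the planned mean, SD and intervals are the same either way.

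Much of this stands. The mean is a plausible intention, and no estimate or comparison is biased by the wording. But the article never ties the criterion to the mean. The endpoint just before it is defined per site, and the planned prediction intervals describe individual sites as well as the average, so the analysis text does not settle the matter. The analysis plan is not shown and may fix the reading. The objection here is not to a missing detail, however, but to a stated threshold that conflicts with the article's own planning figure.

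A reader might go further and infer any of the following. The documents support none of them.

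- *The pilot fails whatever happens.* It does not: under Poisson the literal criterion is met with probability 0.23 at a mean of 15 and 0.90 at a mean of 20.
- *About half the sites must fall below 10.* That is an expectation under an assumed distribution; a mean of 10 does not force it.
- *A missed criterion means that no confirmatory trial is feasible.* The rule concerns a confirmatory study without major design changes, so missing it may only point to redesign.
- *The reading will be chosen after the counts are seen.* The wording leaves room for that; nothing shows any such intention.

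**Conclusion.** The point holds as a conflict between the wording of the recruitment criterion and the planned quantity. Taken literally, the criterion has a chance of about 5 in a million of being met when the true mean is the planned 10 (Poisson), and less with between-site variation. At a mean of 15 the chance is about 0.23 (Poisson), or 0.005 or less for CV 0.4 to 0.8. Taken as a mean, it is met with probability about 0.5 at plan.

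These figures rest on independent sites and an assumed spread, since the article gives none. At the planned mean the conclusion is the same over every spread tried, including an SD of 1 patient; well above plan, the size depends strongly on the spread. They also treat 10 as the true mean, whereas the article presents 200 as a reasonably achievable expectation. The finding is not that the authors intended a per-site minimum, but that the text as written says something the plan cannot be expected to deliver and does not say which reading decides the primary objective.

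**What to change.** Before site counts are analysed, restate the recruitment criterion along these lines: mean enrolment over all 20 randomised sites, with sites that recruit nobody counted as zero, of at least 10 patients in 6 months, judged on the point estimate and reported with its 95% CI. Report the share of sites that reach 10 as a description, not as part of the decision.

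Add an acknowledgement that the threshold equals the planned mean, so the chance of meeting it is about 0.5 if the true mean is exactly 10. The rewording removes the near-certain failure of the literal reading; it does not remove this feature, and readers should know it when they interpret a narrow miss or a narrow pass.

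The cost is a sentence or two in the protocol and the analysis plan. Procedures, data collection, sample size and the planned summaries do not change.
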